### Safety assessment

2.9

During the study, observations and records will be made of any potential adverse reactions, such as bleeding caused by acupuncture, hematoma, needle sickness, pain at the acupuncture site, infection, as well as skin rupture and infection after moxibustion. The primary records will include the incidence rate of adverse events and the grading of safety evaluations. Adverse events will be graded according to the Common Terminology Criteria for Adverse Events (CTCAE) Version 5.0. Mild (Grade 1): asymptomatic or mild symptoms, requiring no intervention; Moderate (Grade 2): symptoms are evident and require non-invasive treatment (such as local hemostasis, disinfection, etc.); Severe (Grade 3 and above): symptoms are severe, requiring hospitalization or leading to discontinuation of treatment. The evaluation time points are detailed in Table 1.

### Data collection and management

2.10

After participants sign the informed consent form, researchers will collect personal information such as general demographic information, clinical history, as well as baseline data including the Numbness VAS Score, 10 g Monofilament Test, 40 g Pressure Pinprick Test, JOA Score, Lower Limb Electromyography (H-reflex difference, F-wave conduction velocity, and latency), VAS Score, Traditional Chinese Medicine Syndrome Score, SF-36 (Short Form 36 Health Survey Questionnaire), etc. Outcome measures will be assessed at specified time points and recorded in the CRF. After the trial, two researchers who are not involved in data distribution or outcome assessment will independently extract data from the CRF into an Excel table. A statistician will then perform statistical analysis on this data after careful review and confirmation. To protect participant privacy, personal names will be replaced with a combination of numbers and initials. Researchers shall keep the data confidential for 5 years after the trial termination. To reduce participant dropout rates, researchers will call participants 2 days before treatment to inquire about their condition and encourage them to receive treatment as scheduled.

### Quality control

2.11

A coordination management team, led by the project leader, shall be established, with dedicated trial auditors and inspectors responsible for trial management and quality control. To minimize bias in human operations, all researchers involved will undergo training. The entire research process will be supervised and inspected to ensure that all operations are carried out by standard operating procedures and that the recording and reporting of research data, treatment procedures, outcome assessments, management of investigational drugs, adverse events, etc., are filled in truthfully, accurately, and completely. Prompt measures will be taken to address any identified quality issues. The scientific research office of the project undertaking unit shall bear the responsibility for project management.

### Statistical analysis

2.12

Sample size calculation was performed using PASS software (version 15.0, NCSS LLC). Based on preliminary data, the estimated mean (standard deviation) of the VAS numbness score after intervention for the treatment group (UA + WA) is 1.6 ± 1.0 cm, and for the control group (electroacupuncture) it is 2.41 ± 1.68 cm. To detect a between-group difference of 0.81 cm with 90% power (*β* = 0.10) and a two-sided *α* of 0.05, at least 41 participants are required in each group. Considering a 15% dropout rate, the final sample size is set at 48 participants per group (96 participants in total). This calculation complies with the CONSORT guidelines for randomized controlled trials.

All analyses will follow the intention-to-treat (ITT) principle, including all randomized participants. Additionally, for sensitivity analysis, a per-protocol set (PPS) analysis will be conducted, excluding participants with major protocol deviations (e.g., fewer than 8 acupuncture sessions, and use of prohibited medications). The primary outcome, the change in VAS numbness score over time points (baseline, 1 week, 4 weeks, 12 weeks, 24 weeks), will be assessed using a linear mixed-effects model (LMM). The model will include group, time, group-by-time interaction, and baseline VAS score as fixed effects. Random intercepts and slopes will account for within-individual variability. Missing data will be handled using multiple imputation (MI) with fully conditional specification (FCS) in SAS 9.4 (SAS Institute), generating 10 imputed datasets. Estimates will be combined according to Rubin’s rules. Sensitivity analysis will compare MI with the last observation carried forward (LOCF). For secondary outcomes with continuous variables (e.g., JOA, SF-36), the same LMM structure as the primary outcome will be used. For ordinal/categorical variables (e.g., TCM syndrome score), proportional odds logistic regression or generalized estimating equations (GEE) will be applied to longitudinal ordinal data. For binary outcomes (e.g., adverse events), comparisons between groups will be made using the chi-square test or Fisher’s exact test (for small sample sizes). Risk ratios (RR) and 95% confidence intervals (CI) will be reported.

The success of assessor blinding will be evaluated using James’ blinding index. A value close to 0.5 indicates effective blinding (0 = completely unblinded; 1 = completely blinded). If there are baseline differences (e.g., age, baseline VAS score), adjustments will be made using analysis of covariance (ANCOVA). Pre-specified subgroups (e.g., age < 50 vs. ≥ 50 years, baseline VAS score severity) will be explored using interaction terms in regression models. *p*-values will be adjusted using the false discovery rate (FDR) correction for multiple comparisons for the primary outcome.

Adverse events (AE) will be graded according to CTCAE v5.0. The incidence rates between groups will be compared using the chi-square test (or Fisher’s exact test for rare events). Descriptive analysis will be conducted for serious adverse events (≥ grade 3). Analyses will be performed using SAS 9.4 (SAS Institute) and SPSS 26.0 (IBM Corp). Continuous outcomes will be reported as mean differences (MD) with 95% CI and effect sizes (Cohen’s d). Categorical outcomes will be reported as risk ratios (RR) with 95% CI. Exact *p*-values will be provided for all tests, with a significance level set at *p* < 0.05 for the primary outcome.

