### Sample size

2.5

The VAS score is the primary outcome measure of this trial. Based on the preliminary results from the research team’s earlier trials, the estimated VAS score for the treatment group after intervention is 1.6 ± 1 cm. Based on the data from relevant domestic clinical trials (26) and our preliminary exploratory trials, we predict that the VAS score for the control group is 2.41 ± 1.68 cm. The sample size ratio for the two groups is 1:1. Using PASS15 to calculate the sample size, with a two-sided test set at *α* = 0.05 and *β* = 0.10, and a test power of 0.9, at least 41 participants are needed in each group. Considering a 15% dropout rate, a total of 48 participants will need to be recruited for each group, resulting in a total of 96 participants required.

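### On the protocol's own means and SDs, 41 per group gives about 74% power for 0.81 cm, not the stated 90%

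*Protocol article*

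**What the plan says.** The calculation appears twice, in Section 2.5 (Sample size) and Section 2.12 (Statistical analysis), with the same inputs and the same answer. In Section 2.12 the post-intervention numbness VAS "for the treatment group (UA + WA) is 1.6 ± 1.0 cm" and "for the control group (electroacupuncture) it is 2.41 ± 1.68 cm". The aim is stated as "To detect a between-group difference of 0.81 cm with 90% power" and "a two-sided *α* of 0.05", from which "at least 41 participants are required in each group". Section 2.5 repeats that "at least 41 participants are needed in each group" and adds that allocation is 1:1 and that PASS 15 was used. The inflation for dropout reads "Considering a 15% dropout rate, the final sample size is set at 48 participants per group", which makes 96 in total.

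Neither section mentions a baseline correlation, a variance reduction from repeated measurements, a one-sided test or any other SD.

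**The concern.** Every input to a two-sample comparison of means is printed, so the figure can be checked directly, and 41 looks too small. The standardised difference is about 0.59 (0.81 divided by a root-mean-square SD of 1.38). At two-sided 5% and 90% power that calls for rather more than 60 per group.

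The trial tests superiority over an active comparator, so the stated power governs how a non-significant result will be read. A reader who accepts 90% will think a true 0.81 cm difference would be missed one time in ten. If power is nearer 74%, it would be missed about one time in four, and a null result would carry less weight against a 0.81 cm difference than the protocol implies.

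**Working it through.** **Inputs** (Section 2.12; allocation from Section 2.5)

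- Means 1.6 and 2.41 cm; difference 2.41 − 1.6 = 0.81 cm, which agrees with the text
- SDs 1.0 and 1.68 cm; sum of variances 1.0² + 1.68² = 3.8224
- Two-sided alpha 0.05 (z = 1.960); power 0.90 (z = 1.282); 1:1

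**Attempt to reproduce 41.** Normal approximation with unequal variances:

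n per group = (1.960 + 1.282)² × 3.8224 / 0.81² = 61.2, so 62.

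The noncentral t calculation (Welch) gives power 0.898 at 62 and 0.903 at 63, so it needs 63. The equal-variance t-test also needs 63. The stated 41 is not reproduced and is about one third too low.

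**Power at the planned numbers**

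| n per group | Standard error, √(3.8224/n) | 0.81 / SE | Power, normal approx. | Power, Welch t |
|---|---|---|---|---|
| 41 | 0.305 | 2.65 | 75.6% | 74.3% |
| 48 | 0.282 | 2.87 | 81.9% | 80.9% |

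**Difference detectable with 90% power (Welch):** 1.00 cm with 41 per group and 0.93 cm with 48. The normal approximation gives 0.99 cm at 41.

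**Does another reading give 41?** Normal approximation unless marked:

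| Variant | n per group |
|---|---|
| Two-sided, 90%, SD 1.0 in both groups | 33 |
| Two-sided, 90%, simple average SD 1.34 | 58 |
| Two-sided, 90%, SD 1.68 in both groups | 91 |
| One-sided, 90%, stated SDs | 50 (t: 51) |
| Two-sided, 80%, stated SDs | 46 (t: 47) |
| One-sided, 80%, stated SDs | 37 (t: 37) |
| Two-sided, 75%, stated SDs | 41 |

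Of these, only 75% power lands on 41, and that contradicts the stated 90%. Working backwards, 41 per group would give 90% power if the common SD were about 1.12 cm (t) to 1.13 cm (normal approximation).

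**Correlation that would make 41 sufficient.** With ANCOVA-type adjustment the required n is multiplied by (1 − r²). From 62: r = √(1 − 41/62) = 0.58. From 63: r = √(1 − 41/63) = 0.59. If all 48 per group contribute: r = √(1 − 48/63) = 0.49.

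**Dropout line.** 41 / (1 − 0.15) = 48.2, which rounds up to 49. In the other direction, 48 × 0.85 = 40.8, just under the stated minimum of 41.

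**The case against.** The strongest reply is that the primary analysis is not a t-test at one visit. Section 2.12 specifies a linear mixed model over five time points with baseline VAS as a covariate, and such a model can be more powerful than a comparison of raw post-treatment means. It follows that the true power of the planned analysis cannot be computed from the document, and that what is shown is a calculation that does not support its own conclusion. That distinction stands. It does not rescue the 41, because the sample-size text uses raw post-intervention SDs and claims no gain from baseline or repeated measures. The correlation needed is not small either, and entry is limited to a baseline VAS of about 40 mm or more, which narrows the baseline range. A value near 0.6 would therefore need justification.

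A second reply is that intention-to-treat analysis with multiple imputation brings all 48 per group into the analysis, so 81% is fairer than 74%. This is right as an upper end: imputation does not restore all the lost information, and 81% is still short of 90%.

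Third, the Discussion admits that sample size may limit power, and results will be reported with confidence intervals that show the imprecision. Both are true, but a general caveat does not correct a specific figure given twice.

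Fourth, the error could lie in a transcribed SD and not in n. The document cannot settle this, so the PASS inputs should be checked first. Finally, the dropout rounding is one patient per group. It is a minor slip, and the main point does not depend on it.

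**Conclusion.** The concern holds. The printed inputs require 62 to 63 evaluable participants per group for 90% power, not 41. On those inputs power is about 74% with 41 per group (75.6% by the normal approximation) and about 81% if all 48 are evaluable. The type II error at 41 is about 26% against the stated 10%.

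This rests on a two-sample comparison of post-intervention means with the stated SDs, 1:1 allocation and two-sided 5%, which is the calculation the protocol describes. It does not exclude that the mixed model reaches 90%, but that would need an assumption the protocol does not state.

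**What to change.** 1. Retrieve the PASS run and confirm which SDs, power and sidedness were entered.
2. If the printed inputs are what was intended, restate Sections 2.5 and 2.12 along these lines: 41 evaluable participants per group give about 74% power (about 81% with 48) to detect 0.81 cm at two-sided 5%; 90% power applies to a difference of about 1.0 cm.
3. If credit for baseline adjustment is intended, state the assumed correlation between baseline and post-treatment VAS and its source. About 0.58 to 0.59 is needed at 41 per group, and about 0.49 if all 48 contribute.
4. Correct the dropout line to n / (1 − 0.15), rounded up.

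This costs protocol wording only: the stated power becomes less favourable and no patients are added. Section 2.14 says enrolment is under way, so the correction should be made before results are known. Should the sponsor prefer to keep 90% power for 0.81 cm without a correlation assumption, the cost is recruitment: 62/0.85 = 72.9 (73) to 63/0.85 = 74.1 (75) per group, or 146 to 150 in total against the planned 96.

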#### Withdrawal and termination criteria

2.3.3

Withdrawal criteria: (1) Individuals unable to complete the entire treatment and observation process; (2) Individuals who cannot fully understand the various forms and questionnaires provided during the study and require assistance; (3) Individuals concurrently receiving other treatments; (4) Individuals with poor compliance; (5) Individuals with incomplete data affecting efficacy and safety evaluation; (6) Individuals experiencing severe adverse reactions or complications who are unsuitable for continued treatment and are therefore withdrawn from the trial; and (7) Individuals who have not completed more than 2/3 of the treatment course (including those withdrawn from the trial and lost to follow-up).

Termination criteria: Participants experiencing severe adverse events or reactions making it inappropriate to continue in the study; major errors found in the study design or significant deviations from the facts; participants who develop serious complications or deteriorate in a condition requiring emergency measures; participants withdrawing from the clinical study; patients who are uncooperative or noncompliant with treatment, despite repeated explanations from clinicians; during the trial, researchers should retain all original trial records and document in detail the reasons and timing for withdrawal. Those who have completed more than half of the treatment regimen should be included in the efficacy statistics.

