### Interventions

2.6

Participants in both groups of this study will be assessed on the first-day post-surgery, with treatment beginning on the second day and continuing for three consecutive days, totaling three sessions, with needles retained for 30 min each time. Subsequently, the treatments will be conducted three times a week for 4 weeks. Both treatments will be administered by trained acupuncturists who hold a valid practitioner certificate and have over 5 years of clinical experience, having undergone standardized training before the trial to ensure consistency. After discharge, patients need to undergo acupuncture treatment in the outpatient department; if numbness symptoms disappear, acupuncture treatment should be halted, and follow-up will continue per the experimental protocol.

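### Participants who stop acupuncture before the eighth session because their numbness has gone, as the protocol instructs, are dropped from the per-protocol set as major deviators

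*Protocol article*

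**What the plan says.** Section 2.6 (Interventions) sets the course in two blocks. The first runs daily, "continuing for three consecutive days, totaling three sessions, with needles retained for 30 min each time". The second follows: "Subsequently, the treatments will be conducted three times a week for 4 weeks". The same section gives the stopping instruction: "if numbness symptoms disappear, acupuncture treatment should be halted, and follow-up will continue per the experimental protocol".

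Section 2.12 (Statistical analysis) makes intention-to-treat the main approach: "All analyses will follow the intention-to-treat (ITT) principle, including all randomized participants". It then adds that "for sensitivity analysis, a per-protocol set (PPS) analysis will be conducted". Who belongs to that second set is fixed by what it leaves out, namely by "excluding participants with major protocol deviations (e.g., fewer than 8 acupuncture sessions, and use of prohibited medications".

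Section 2.3.3 (Withdrawal and termination criteria) holds two further session-based rules. Item (7) of the withdrawal list covers "Individuals who have not completed more than 2/3 of the treatment course". The section's last sentence reads "Those who have completed more than half of the treatment regimen should be included in the efficacy statistics".

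None of the three sections makes an exception for a participant who stopped because numbness resolved.

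**The concern.** Sections 2.6 and 2.12 collide for anyone whose numbness disappears before the eighth session. Under 2.6 that person is doing what the protocol asks. Under 2.12 the same person has committed a major deviation and leaves the per-protocol set.

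The exclusion is not neutral. Section 2.8.1 defines a numbness VAS of 0 as no numbness, which is the best score on the primary scale. The session cut-off therefore removes people because of their result on the endpoint being analysed. The per-protocol set is the only alternative analysis population the article names, since the comparison of multiple imputation with LOCF concerns missing data only. If its result differs from the intention-to-treat result, the gap could be read as a sign of fragility, and agreement could be read as robustness. In either case part of the result could be produced by the exclusion rule.

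**Working it through.** **Inputs.** Session schedule, 2.6. Cut-off of 8 sessions, 2.12. Two-thirds and one-half rules, 2.3.3. Planning means of 1.6 cm (treatment) and 2.41 cm (control), 2.5 and 2.12. VAS 0 = no numbness, 2.8.1. The shares of early resolvers are assumptions, because the article gives none.

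**Step 1: who is affected.** The planned course is 3 + 3 × 4 = 15 sessions. If the first block is counted inside the four weeks, it is 3 + 3 × 3 = 12. Eight sessions is 8/15 = 53% or 8/12 = 67% of the course. More than two-thirds means more than 10 of 15, or more than 8 of 12. More than half means at least 8 of 15, or at least 7 of 12. Read literally, an instructed stop is handled as follows:

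| Course | Stop after session | Per-protocol set (2.12) | Withdrawal item 7 (2.3.3) | More-than-half rule (2.3.3) |
|---|---|---|---|---|
| 15 | 1–7 | excluded | listed | not met |
| 15 | 8–10 | kept | listed | met |
| 15 | 11–14 | kept | not listed | met |
| 12 | 1–6 | excluded | listed | not met |
| 12 | 7 | excluded | listed | met |
| 12 | 8 | kept | listed | met |
| 12 | 9–11 | kept | not listed | met |

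The per-protocol exclusion affects stops after 1 to 7 sessions, roughly the first 2 to 2.5 weeks. Later complete responders stay in.

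**Step 2: the planned difference.** 2.41 − 1.6 = 0.81 cm, as 2.12 states.

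**Step 3: effect of removing early resolvers.** Assume those removed would score 0 at the time analysed. Taking a share f of zeros out of an arm with mean m leaves a mean of m/(1 − f). The per-protocol difference is then

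2.41/(1 − f_C) − 1.6/(1 − f_T).

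| Removed, treatment/control | Treatment mean | Control mean | Difference (cm) | Change from 0.81 |
|---|---|---|---|---|
| 15% / 5% | 1.882 | 2.537 | 0.65 | −19% |
| 20% / 5% | 2.000 | 2.537 | 0.54 | −34% |
| 5% / 5% | 1.684 | 2.537 | 0.85 | +5% |
| 5% / 10% | 1.684 | 2.678 | 0.99 | +23% |

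**Step 4: direction.** Setting the formula equal to 0.81 gives 2.41 × f_C/(1 − f_C) = 1.6 × f_T/(1 − f_T). In this simple model the difference shrinks only if the odds of early resolution in the treatment arm exceed 2.41/1.6 = 1.51 times those in the control arm. Otherwise it grows, even with equal shares.

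**Step 5: with the exemption.** If instructed stops count as adherent, nobody leaves the set for following 2.6, and this source of change disappears.

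**The case against.** Several points on the other side have weight.

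- *The primary result is safe.* A reader might infer that the trial's main conclusion is biased. It is not: 2.12 keeps all randomized participants in the main analysis, and the per-protocol set is a sensitivity analysis. This stands and limits the point.
- *Most complete responders may be kept.* It is tempting to say that the rule removes the best responders as a class. The documents do not support that, because anyone stopping after eight or more sessions is retained. This also stands.
- *The direction is unknown.* One might infer bias against the experimental arm. No early-resolution rate is given. Entry requires a numbness VAS of at least 40 mm (2.3.1), and the Introduction reports that numbness recovers more slowly than pain, so shares of 15–20% may be high. A rough normal approximation to the planning values puts Φ(−1.6/1.0) = 5.5% of the treatment arm and Φ(−2.41/1.68) = 7.6% of the control arm at or below 0. Removing those shares gives 2.607 − 1.693 = 0.91 cm (+13%), the opposite direction to the first two scenarios. The approximation is poor on a bounded scale, but it shows that no direction can be claimed.
- *The cut-off is only an example, and the analysis plan may refine it.* The deviations are introduced as examples, and the Abstract mentions a predefined analysis plan that is not shown. But the article states a numeric threshold without qualification, and that threshold conflicts with its own instruction. This is a rule fixed badly, not a detail left out. The objection weakens the point without removing it.
- *Item (7) of 2.3.3 may be aimed at dropouts.* Its own parenthesis mentions withdrawn and lost participants, and 2.6 expressly keeps resolved participants in follow-up. So it cannot be said that early resolvers are in fact withdrawn, only that the sections do not agree.

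**Conclusion.** The point holds within limits. As written, 2.12 classes a participant who stops before the eighth session under 2.6 as a major deviator, and this makes per-protocol membership depend on the primary outcome. The defect lies in the rule and does not need any particular resolution rate.

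Its size cannot be derived from the article. Over the assumed shares shown, the per-protocol difference runs from 0.54 to 0.99 cm against a planned 0.81 cm. These figures assume that those removed score 0 at the time analysed. They also use a single post-treatment mean, whereas the planned analysis is a baseline-adjusted mixed model over visits to 24 weeks, so they are illustrations and not predictions. The intention-to-treat analysis is unaffected. This is a worthwhile correction to a supporting analysis and does not threaten the main inference.

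**What to change.** In 2.12, define per-protocol adherence against the sessions due under the protocol. A participant halted under 2.6 because numbness resolved is then judged on the sessions due up to that point, and the stop itself is not a major deviation. Record the date and reason for halting acupuncture, as 2.7 already has the stopping of the basic drugs recorded.

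Reconcile 2.3.3 with 2.6 and 2.12, so that the two-thirds withdrawal criterion, the more-than-half rule for efficacy statistics, the 8-session cut-off and the intention-to-treat statement no longer classify the same participant differently. State the total number of planned sessions there too, since the fractions depend on it.

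The cost is a sentence or two in 2.12, a clarification in 2.3.3 and one recorded field. Sample size and the primary analysis do not change. Section 2.14 says enrolment is under way, so the change should be made as a documented amendment before anyone sees results by arm. Redefining the set later would look data-driven.

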**Objective:**

This proposed trial aimed to evaluate the effectiveness and safety of UA (umbilical acupuncture) combined with WA (warm needle acupuncture) in treating residual numbness after LDH surgery. To verify the hypothesis that the combined method is superior to traditional electroacupuncture.

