According to domestic literature reports, electroacupuncture has a definite therapeutic effect in treating residual pain and numbness after percutaneous transforaminal endoscopic discectomy (PTED) for LDH. The overall effective rates for pain and numbness relief are 95.45 and 92.86%. The overall efficacy of combined electroacupuncture treatment is superior to that of Western medicine treatment alone (37). Some other articles have reported that low-frequency EA was applied directly to the spinal nerve root at right L4, L5, and, S1, immediately after treatment, right or left back and lower extremity pain and numbness were markedly reduced. The walking distance of patients was also greatly extended. The mechanisms underlying this effect may be attributed to inhibitory control at the spinal level, inhibition of potential activity by hyperpolarization of nerve endings, or changes in nerve blood flow (38, 39).

Therefore, we have established an electroacupuncture control group. We will compare this treatment with electroacupuncture therapy to explore a potentially more effective acupuncture treatment regimen that promotes early rehabilitation for patients with numbness after LDH surgery. We hope to find a better acupuncture treatment method to guide clinical practice and improve treatment outcomes. In addition, this study may provide more scientific evidence for non-pharmacological treatments and facilitate future related research.

This study has certain limitations. Its single-center design may not fully represent the clinical practice situation across multiple centers. The VAS (Visual Analog Scale) score is a subjective outcome measure that is susceptible to individual differences and psychological factors among patients. The follow-up period of this study is 6 months, which may not be sufficient to fully assess the long-term effects of the treatment. Insufficient sample size may affect the statistical power of the results, and there may be issues with poor patient compliance and high dropout rates in the study.

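### The primary mixed model leaves the coding of time and the superiority contrast open; read with linear time, its group-by-time test has roughly 0-30% power for an early effect of the size planned for

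*Protocol article*

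**What the plan says.** The Objective in the Abstract is a superiority claim: "To verify the hypothesis that the combined method is superior to traditional electroacupuncture". Section 2.12 defines what is analysed: "The primary outcome, the change in VAS numbness score over time points (baseline, 1 week, 4 weeks, 12 weeks, 24 weeks". The fixed and random parts of the model are given as "The model will include group, time, group-by-time interaction, and baseline VAS score as fixed effects. Random intercepts and slopes will account for within-individual variability". JOA and SF-36 take the same structure.

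Section 2.5 sizes the trial on one comparison: "the estimated VAS score for the treatment group after intervention is 1.6 ± 1 cm", and for the other arm "we predict that the VAS score for the control group is 2.41 ± 1.68 cm". Section 2.12 repeats this as a difference of 0.81 cm, to be detected with 90% power at two-sided 5% with 41 evaluable patients per arm.

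Three other statements bear on the reading. Section 2.12 plans a false discovery rate correction for the primary outcome and reports continuous outcomes as mean differences with Cohen's d. The Discussion looks for a regimen that "promotes early rehabilitation for patients with numbness after LDH surgery".

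**The concern.** A random slope needs a numeric time variable, and analysts ordinarily put the same variable in the fixed part. Group-by-time then asks whether two straight lines through the visits have equal slopes. That is a different question from whether numbness is lower after the course.

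The plan's own figures suggest that a straight line is the wrong shape. Patients enter at about 4 cm or more (2.3.1) and are expected at 2.41 or 1.6 cm after treatment. Taking that as week 4, a control mean starting at 4 cm falls (4 - 2.41)/4 = 0.40 cm per week. At that rate it would reach zero 2.41/0.40 = 6 weeks later, near week 10. The curve must therefore flatten during follow-up.

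At stake is whether a treatment with the sized effect is recognised, and whether a faster recovery that control later matches is estimated in the wrong direction.

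**Working it through.** **1. The plan's figure.** The average variance is (1.0² + 1.68²)/2 = 1.911. Then n = 2 × (1.960 + 1.282)² × 1.911 / 0.81² = 61.2, so 62 per arm, not 41. That is a separate matter; 41 is kept below because it is the plan's number. At 41 per arm the unadjusted comparison has z = 0.81/√(3.822/41) = 2.653 and power Φ(2.653 - 1.960) = 76%. With an assumed baseline correlation of 0.5, z = 2.653/√(1 - 0.25) = 3.063 and power is 86%.

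**2. Leverage under linear time.** For t = 0, 1, 4, 12, 24 the mean is 8.2 and the squared deviations are 67.24, 51.84, 17.64, 14.44 and 249.64, total 400.8. Week 24 holds 62% of this and weeks 12 and 24 together 66%.

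**3. Slope of the between-group difference, Σ(t - 8.2)d / 400.8.**
- Held benefit, d = 0, -0.4, -0.81, -0.81, -0.81: -9.59/400.8 = -0.024 cm per week, or -0.57 cm over 24 weeks.
- Benefit lost by week 24, d = 0, -0.4, -0.81, -0.4, 0: +4.76/400.8 = +0.012 cm per week, which favours control. This sign follows from the assumed profile and needs no correlation or variance.

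**4. Simulated power, 41 per arm.** From the plan: 2.41 cm, 0.81 cm, SDs 1.68 and 1.0, visit times. Assumed: control means 6, 4.8, 2.41, 2.41, 2.41 cm; the same SDs at every visit; correlation 0.5; extra slope SD 0 or 0.05 cm per week. Model: REML with random intercept and slope and baseline as covariate. There were 150 runs per case, so Monte Carlo error is about 2-4 points. Pairs are results with baseline in the response / weeks 1-24 only. Linear power is in favour of the combined treatment.

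| Benefit (cm) at 0, 1, 4, 12, 24 weeks | Linear group-by-time | Joint categorical group-by-time |
|---|---|---|
| 0, 0.20, 0.81, 0.81, 0.81 | 21-27% / 9-11% | 70-82% / 43-51% |
| 0, 0.81, 0.81, 0.81, 0.81 | 5-8% / 0-1% | 77-81% / 4-5% |
| 0, 0.20, 0.81, 0.65, 0.41 | 2% / 0-1% | 64-69% / 35-37% |
| 0, 0.20, 0.81, 0.40, 0 | 0% / 0% | 72% / 52-57% |

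With categorical fixed time and the same random slopes, the week-4 contrast has 89-90% / 85% in every row.

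**5. Sensitivity.**
- Control means 6.0, 4.6, 2.41, 2.0, 1.8 cm, correlation 0.5-0.7, 500 runs: the linear test has 10-16% / 4-5% for a held benefit and 0% for one fading to zero. With post-baseline data only, fading to zero was significant for control in 28-31% of trials. A baseline-adjusted week-4 comparison had 76-87%. Under no effect the linear test rejected in at most 0.4%, because the curvature is absorbed into the error variance.
- The same means at correlation 0.6, 130 runs: 12% / 4% (held), 0% (fading to zero), and 85-91% for the week-4 contrast.
- Starting level, held benefit, correlation 0.5, 120 rough runs: 17% from 6.0 cm, 26% from 5.0 cm, 33% from 4.5 cm with lower late means.
- A benefit that keeps growing to week 24: 78-83% with baseline in the response.
- Analytic power over weeks 0-24 if a straight line did fit, slope SD 0-0.04: 42-91% (builds to week 4, holds) and 19-51% (full by week 1, holds).

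**The case against.** The strongest reply is that the plan never says time is linear and never makes the interaction the primary test. A reader might infer from the random slope that the trial is committed to comparing straight-line rates, and that a treatment with the sized effect would therefore usually be declared not superior. The document does not support that. Categorical time in the fixed part with a numeric slope in the random part satisfies the same sentence. Five listed visits, a multiplicity correction for the primary outcome and mean-difference reporting fit visit-wise comparisons at least as well, and a week-4 contrast is then well powered. This part of the reply stands.

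It also stands that the low figures are conditional. The plan gives no week-12 or week-24 means, no correlations and no fading, and power is higher where a straight line fits.

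A further reply is that the coding of time is commonly left to an analysis plan that is not shown. Silence alone would indeed be no finding. But the article does fix random slopes and a group-by-time term, which invite the linear reading, while it sizes the trial on a single post-treatment difference. Categorical coding alone does not settle it either: with baseline used only as a covariate, the joint interaction has 4-57% power, because a benefit held from week 1 sits in the group term.

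**Conclusion.** The point holds conditionally. The stated model admits readings whose power for the planned effect runs from about 0% to about 90%, and nothing in the article selects among them. With time linear in weeks and group-by-time as the test, power for an effect present by week 4 that then holds or fades is roughly 0-30%. An effect that fades to zero yields an estimate favouring control. With categorical time, a week-4 contrast keeps about 85-90% (76-87% in one set of assumptions). These ranges assume 41 per arm, that after intervention means week 4, a curve that flattens after treatment, and correlations of 0.5 to 0.7. They do not show that the trial as planned has low power; they show that one natural reading of its model would.

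**What to change.** In 2.12, replace the sentence on random intercepts and slopes with wording such as: *Time is a categorical factor (visits at 1, 4, 12 and 24 weeks as labelled in Table 1). Within-patient covariance is unstructured and no linear slope is fitted. Superiority is tested by the baseline-adjusted between-group difference in mean numbness VAS at the end-of-treatment (4-week) visit; the other visits are supporting estimates.* Use the same structure for JOA and SF-36. Categorical time also removes any dependence on the visit clock: Table 1 dates the last two visits from the end of treatment and 2.12 does not, so a numeric axis could end at 24 or 28 weeks.

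Visits and enrolment do not change. Four visits need 4 × 5/2 = 10 covariance parameters, or 20 if they differ by arm. The larger cost is one of substance: the primary conclusion then rests on one visit, whereas 2.12 now describes change over all visits to 24 weeks. The sponsor should make that choice knowingly, and before any unblinded look at the data. It matches the quantity on which the trial was sized.
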